### Intervention

The implemented stress management training is based on the successfully conducted intervention of the MAN-GO project [48]. It is going to be adapted based on the results of a previous (and still ongoing) needs analysis concerning format and content. Depending on the results, it will most likely obtain the following modules:
Stress: effects of stress, individual stress symptoms, mentalization ability under stressWork stress models: gratification model, demand-control-model, organizational fairnessLeadership: stress-preventive, health-oriented, and relational leadership, leaders as role models, new demands on leaders based on COVID-19 and the digitalizationShort term relief: brooding strategies, attention guidingConflict management: dealing with (emotional) conflicts and catch-22 situations at the workplaceRelaxation: progressive muscle relaxation, 1-min meditationResources: sweet spot imagination, social support, 10 fingersCase work: working on cases brought in by participants, approach based on Balint groups and collegial case adviseOptional additive online modules: impact of stress on cardiovascular diseases, further stress symptoms

Trainings are going to take place in groups with 8–12 leaders and are held by two trainers. As far as possible in the context of COVID-19, they should be carried out in persona. Concerning the didactical frame, the trainings consist of a mixture of lectures, open discussions as well as single, peer, and group work. Trainings will take place in Ulm and surrounding as well as in Tuebingen and surrounding.

### Outcome variables

All measurements will take place in Germany. More specifically, participants are recruited in Ulm and Tuebingen and their surroundings. Participants are allowed to answer all questions from any suitable place, as questionnaires and further items are provided online. For the physiological measures (leaders only), appointments in Ulm and Tuebingen are going to be arranged.

#### Leaders

Leaders are going to be asked to complete single items, 9 questionnaires and three physiological measures.

##### Single items

*Sociodemographic data.* Participants are going to be asked for their gender, age, marital status, children living in the household and the highest educational level attained. Furthermore, the monthly net income can be entered voluntarily and the number of personal dependants.

*Work-related data.* Regarding the professional situation, it is asked to indicate the branch, current position, need to do shift work and number of employees to be supervised. Furthermore, the average working time and break times as well as unpaid overtime are enquired.

*Health-related data.* Days of incapacity to work in the last 3 or 12 months, activity in everyday working life, weight and health behaviour (cigarette and alcohol consumption) are going to be recorded.

##### Questionnaires

All subsequent questionnaires are collected at three measurement times (T_0_, T_1_, T_2_). The target outcome is the change in the intervention group compared to the waiting control group over time.

*Perceived Stress-Reactivity-Scale* [52]. The PSRS assesses perceived stress reactivity on 5 scales: reactivity to social assessment (5 items, “If I am wrongly criticized by others ...”), reactivity to failure (4 items, e.g., “If I did something wrong ...”), reactivity to social conflict (5 items, e.g., “When I argued with other people ...“), reactivity to work overload (5 items, e.g., “When I have little time for my work ...”) and prolonged reactivity (4 items, e.g., “When I have free time after strenuous work ...“). In addition, an overall score can also be calculated. All items are answered by agreeing with one of three default answers. Scale reliability is sufficiently high and varies between α = .79 and α = .82 with α = .89 for the total score (Cronbach’s Alpha).

*Effort Reward Imbalance Questionnaire (ERI,* [53]). The ERI conducts self-assessments of psychosocial workloads on three scales: exertion (6 items, e.g., “I am often interrupted and disturbed in my work”), reward (11 items, e.g., “I get the recognition I deserve from my superiors”) and over-commitment (6 items, e.g., “Those who are closest to me say I sacrifice myself too much for my job”). Reward is a multidimensional concept and consists of the following subscales: recognition, pay/progression and job security. The exertion and reward dimensions are assessed with five-point Likert-scale, ranging from “unexposed to adverse condition” (1) to “exposed to adverse conditions and very distressed” (5). Over-commitment is measured with a four-point Likert-scale, ranging from “Strongly disagree” (1) to “Strongly agree” (4). The internal consistency of the scales is sufficiently high and between α = .62 and α = .90 (Cronbach’s Alpha).

*Hospital Anxiety and Depression Scale (HADS, Herrmann, 1997).* The HADS is a 14-item questionnaire (7 items each for anxiety and depression) for self-assessment of depressive (e.g., “I still enjoy the things I used to enjoy”) and anxiety symptoms (e.g., “Worrying thoughts go through my mind”). All items are answered by agreeing with one of four default answers. Scale reliability is high with α = .86 for anxiety and α = .91 for depression (Cronbach’s Alpha).

*Leader-Member Exchange 7 (LMX-7, Graen & Uhl-Blen, 1995).* The LMX-7 questionnaire consists of 7 items assessing the relationship between leaders and employees (e.g., “How well do you understand the work-related problems and needs of your employees?”) on a 5-point Likert-Scale. Cronbach’s Alpha is high: α = .84 [54].

*Occupational Self-Efficacy Expectations – short scale (*Berufliche Selbstwirksamkeits-erwartung, BSWE*, Schyns & von Collani, 2014).* The BSWE *–* short scale consists of 8 items measuring occupational self-efficacy expectations (e.g., “When unexpected situations arise at work, I always know how to act”) with a 6-point Likert-Scale ranging from “completely true” (1) to “not true at all” (6). Scale reliability is high with α = .84 (Cronbach’s Alpha).

*Psychosocial Safety Climate Questionnaire 4 (PSC-4,* [55]). The PSC-4 is a short questionnaire with only 4 items measuring the Psychosocial Safety Climate at work (e.g., “Senior management show support for stress prevention through involvement and commitment”). All items are answered using a 5-point Likert-Scale, ranging from “strongly disagree” (1) to “strongly agree” (5).

*Operationalized psychodynamic diagnosis structure questionnaire (OPD-SF, Ehrental* et al.*, 2012).* The OPD-SF assesses the Axis 4 (Structure) from the Operationalized Psychodynamic Diagnostic system (OPD). Only two of the five dimensions are used for the purpose of this study: self-awareness (12 items, e.g., “I often have feelings that I cannot understand”) and self-regulation (13 items, e.g., “When I’m very upset, I often act rashly”). Items are measured on a five-point Likert-scale ranging from “strongly disagree” (1) to “strongly agree” (5). Cronbachs α ranges from .88 to 91 (self-awareness) and .82 to .84 (self-regulation) [56].

*Client Sociodemographic and Service Receipt Inventory (CSSRI,* [57]). The use and costs of health care resources will be estimated by means of the CSSRI adapted for the application in the target population [57].

*EuroQol’s questionnaire for health related quality of life (EQ-5D 5 L,*[58]*).* Health-related quality of life will be assessed by means of the EuroQol EQ-5D 5 L. The EQ-5D 5 L defines subjective health states at the following five dimensions Mobility, Self-care, Usual activities, Pain and discomfort, Anxiety and depression at a five-level scale [58]. The individual health states will be evaluated by means of country-specific representative preference based value sets [59].

##### Physiological measures

*Hair cortisol.* As a first biological stress parameter, the content of hair cortisol (determined via a 2 cm long hair strand) as an indicator for the hypothalamic-pituitary-adrenal axis is going to be collected. Several thin hair strands will be cut as close as possible to the scalp from the posterior vertex region of the head. For determination of hair cortisol concentrations, the first scalp-near 2 cm segment will be used which is thought to reflect the cumulative cortisol secretion of the past 2 months [60]. Hair wash and cortisol extraction procedures are based on a laboratory protocol by Stalder et al. [61], with minor modifications. In brief, hair samples will be washed twice for 3 min using 3 mL isopropanol. For cortisol extraction, 10 ± .5 mg whole, finely cut hair will be incubated in 1.8 mL methanol for 18 h at room temperature. After incubation 1.6 mL will be transferred in another glass vial. Then, 1.6 mL of the supernatant is evaporated at 50 °C until samples are completely dried. Finally, the samples will be resuspended with 225 μL HPLC ultra-pure water and vortexed for 20 s. For cortisol determination, a commercially available cortisol luminescence immunoassay will be used (LIA; IBL International, a Tecan Group company, Hamburg, Germany).

*Saliva alpha-amylase.* As a second biological stress parameter, alpha-amylase activity in saliva is measured as basal activity of the sympathetic nervous system [62, 63]. Using SaliCaps (IBL International, a Tecan Group company, Hamburg, Germany), participants will be asked to not swallow for 2 min and then transfer all accumulated saliva in pre-labelled vials. Furthermore, they will be asked to provide information on meals and drinks 2 h prior to saliva collection in order to control for confounding variables. The saliva samples will be stored as cool as possible in the participants’ fridge or freezer and are then at the earliest convenience stored at − 80 °C in freezers of the University. Salvia alpha-amylase activity will be measured using a kinetic colori metric test (for details, see also [64]) and reagents obtained from DiaSys Diagnostic Systems (Holzheim, Germany). Saliva will be diluted 1:400 using 0.9% saline solution. The reagents contain the enzyme alpha-amylase in a specified amount and alpha glucosidase, which converts the substrate ethylidene nitrophenyl to p-nitrophenol. The rate of formation of p-nitrophenol is directly proportional to the samples’ amylase activity and is detected using an absorbance reader at 405 nm (Biotek Synergy HTX, BioTek Instruments, Winooski, VA, USA).

*Heart rate variability.* A 24-h measurement of heart rate variability is collected using a Faros 180 ECG monitor with a textile belt. Circadian parameters of 24 HRV measures will serve as an indicator of mental health and stress perception ([65, 66]; Williams et al., 2018).

*Satisfaction with the training.* Participants are going to be asked to evaluate their trainers (8 questions each, 6-point Likert-scale) and the training (12 questions, 6-point Likert-scale) concerning acceptance and satisfaction.

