## Method

### Population and sample size

#### Leaders

The target group are leaders of small and medium-sized enterprises (SMEs). We define SMEs as enterprises with up to 500 employees [50, 51] without regarding the annual sales. Leaders of all genders aged between 18 and 65 years are allowed to participate as long as they are not about to retire within the next year. A sample size of *n* = 100 participants in the intervention group and *n* = 100 participants in the waiting control group is planned (*N* = 200 participants).

The sample size calculation was performed using G*Power3.1. Based on a 2 × 3-mixed design (factor 1 (group): intervention or waiting control group; factor 2 (point in time): baseline, 6 months and 12 months later) the required sample size for a MANOVA with measurement repetition was estimated using the following predefined parameters: mean effect size f = .25 (Ω = 0.06), α-error = .05, test strength 1-β = .80. This results in a required sample size of *n* = 158 participants (*n* = 59 per group). The calculation of the required sample size was based on the procedure proposed by Prajapati et al. (2010) to calculate the required sample sizes for all possible effects (within, between, interaction) of the present design and to use the largest calculated sample size. Due to the high effort of the outcome criteria to be collected (e.g., saliva samples, 24-h heart rate variability) a high lost-to-follow-up as well as numerous missing values can be expected. We therefore calculate with a total failure rate of 21% (lost-to-follow-up and due to missing values), resulting in a required sample size of *N* = 200 (*n* = 100 per group at T_0_).

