### Data collection, management, and analysis

*Data collection.* Leaders’ sociodemographic and work-related data will be assessed at baseline before the intervention. The self-report measures of health-related indices, perceived stress (PSRS-23 [52]), work satisfaction (ERI [53]), symptoms of depression and anxiety (HADS-D [74]) and well-being (WHO-5 [75]) will be assessed at three different points of time: at baseline, at a 6-month-follow-up post-intervention and a 1-year-follow-up. The questionnaires can be filled in at home or during the clinic visits, where the physiological data will be recorded across the three time points. All questionnaire data will be assessed online via the encrypted German Unipark servers. Physiological measures, i.e. hair cortisol, saliva samples for alpha-amylase activity and blood pressure will be collected by a trained study nurse on site. To assess the 24-h-heart rate variability, participants will wear a belt for 24 h after their appointment at the clinic. Employees will receive online questionnaires that can be filled in during work in order to rate their individual stress levels and their perceived interaction with their leaders. Data will be transmitted electronically across encrypted German servers provided by the online assessment tool Unipark.

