#### Statistical methods

Data will be analysed using the statistic software IBM SPSS Statistics 27. Descriptive analyses will be conducted after the baseline. A multivariate analysis of variance (MANOVA) with all relevant outcome parameters as specified above will be calculated in order to test the effects of the intervention on different dependent variables. Potential covariates will be included in the analysis. Therefore, if relevant covariates occur, a MANCOVA will be performed instead of the MANOVA. A covariate will be identified as such, if a demographic variable will correlate with the outcome variable or if there is a significant difference between the intervention group and the waitlist control group across this variable.

To evaluate the effects of the stress management intervention more specifically, changes in outcome variables will be analysed by two-factorial ANOVA with repeated measures and group (intervention vs. waiting control group) as a between-person effect. The core hypothesis is that perceived stress and physiological stress parameters of leaders will significantly decrease from baseline to follow-up measurements for participants in the intervention group. Thus, we will test the interaction effect of time x group for the different outcome variables. Where necessary, Bonferroni correction will be applied to avoid inflation of the type one error by multiple comparisons.

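### Meal and drink data are collected to control confounding of salivary alpha-amylase, but the analysis as written has no place for them

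*Protocol article*

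**What the plan says.** Under Physiological measures, the saliva paragraph gives the purpose of the intake data: "they will be asked to provide information on meals and drinks 2 h prior to saliva collection in order to control for confounding variables". The same paragraph treats alpha-amylase as a marker of basal sympathetic activity.

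Statistical methods opens with a MANOVA and a general statement that possible covariates will be included, which turns it into a MANCOVA. It then says what qualifies: "A covariate will be identified as such, if a demographic variable will correlate with the outcome variable". The alternative criterion, a significant difference between the arms, refers to that same demographic variable. For the outcome-specific tests, "changes in outcome variables will be analysed by two-factorial ANOVA with repeated measures", with group as the between-person factor and time x group as the effect of interest. The core hypothesis names physiological stress parameters beside perceived stress.

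The article describes the saliva setting in two ways. Data collection has a study nurse taking the samples on site. Physiological measures has them kept in the participant's own refrigerator or freezer until they reach the university.

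**The concern.** The protocol itself calls recent eating and drinking a confounder of alpha-amylase and asks participants for the data needed to deal with it. The covariate rule then leaves those data out, because a meal in the last two hours is not a demographic variable. Widening the rule alone would not be enough: the named models are built for covariates that are fixed for a person, and intake is a feature of the visit.

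The time x group test rests on within-person change. Variation caused by what was consumed before one visit and not before another therefore goes straight into its error term. At stake is the precision of one of the physiological outcomes in the core hypothesis, and a burden on participants whose stated purpose is not served.

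**Working it through.** **1. Can the intake data enter under the stated rule?**

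| Requirement in Statistical methods | Food and drink in the last 2 h |
|---|---|
| Variable is demographic | No |
| It correlates with the outcome, or differs between arms | Not reached, since both criteria apply to a demographic variable |
| One value per person (usual form of a covariate in repeated-measures ANOVA or MANCOVA) | No; it can differ at T0, T1 and T2 |

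The data fail the first requirement as worded and do not fit the third without a workaround.

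**2. The plan's own sample size.** Inputs from Population and sample size, Leaders: "mean effect size f = .25 (Ω = 0.06), α-error = .05, test strength 1-β = .80"; two groups, three time points; 158 leaders before losses; 21% loss. For the repeated-measures MANOVA interaction:

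- df1 = (2 − 1)(3 − 1) = 2
- df2 = N − 3 = 155
- λ = N × f² = 158 × 0.0625 = 9.875
- Power from the noncentral F distribution = 0.802

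So 158 reproduces, and 158 / 0.79 = 200 reproduces the recruitment target. (The printed 59 per group does not match 158 / 2 = 79. That is a separate slip and plays no part here.)

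**3. What could uncontrolled intake cost?** The document gives no variance of alpha-amylase and no share of it due to food or drink, so the values below are assumptions.

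*Case A: intake adds a fraction k to the variance behind f = 0.25.* Then λ = 9.875 / (1 + k).

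| k | λ | Power at 158 | Analysable N for 80% power |
|---|---|---|---|
| 0 | 9.875 | 0.802 | 158 |
| 0.1 | 8.977 | 0.761 | 174 |
| 0.2 | 8.229 | 0.722 | 190 |
| 0.3 | 7.596 | 0.685 | 204 |
| 0.5 | 6.583 | 0.618 | 236 |
| 1.0 | 4.938 | 0.490 | 312 |

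If the 10%, 20% or 30% is instead a share s of the total variance, λ = 9.875 × (1 − s) and power is 0.757, 0.703 or 0.641.

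*Case B: f = 0.25 already contains this noise.* Nothing is lost against the plan. Adjustment that explains a fraction R² of the residual variance gives λ = 9.875 / (1 − R²):

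| R² | λ | Power at 158 |
|---|---|---|
| 0.05 | 10.395 | 0.823 |
| 0.10 | 10.972 | 0.844 |
| 0.20 | 12.344 | 0.886 |
| 0.30 | 14.107 | 0.925 |

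The document does not say which case applies. In both, using the data helps if intake explains variance, and by an amount that cannot be fixed in advance.

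**The case against.** **The intake data are not strictly shut out.** Statistical methods says in general terms that possible covariates will be included, and the section on missing and spurious data allows plausibility checks and exclusion from single analyses. Visit-to-visit differences in intake could also be reduced to one value per person for each change contrast. And how one item is used is often left to an analysis plan. Part of this stands: to say the data can never be used would be too strong. But the general sentence is followed at once by a definition limited to demographic variables, a plausibility check is not adjustment, and the contrast-by-contrast workaround is not what is described. The article chose to state both the rule and the model, and neither matches the purpose given for the data.

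**The power figures are illustrations.** This stands in full. The variance fractions are assumed, and a generic effect size of 0.25 may already include ordinary visit noise.

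**Stronger readings that the document does not support.**
- A reader might infer that saliva and heart rate variability are measured at any hour or weekday, or that eating beforehand is unrestricted. The article gives no such rule either way. It says only that appointments are arranged and that "participants will wear a belt for 24 h after their appointment at the clinic". A condensed article may leave scheduling and pre-sample instructions to the full protocol. Start hour also matters little for a recording that covers 24 hours.
- A reader might extend the point to all physiological outcomes. Hair cortisol reflects about two months and is not sensitive to a recent meal.
- A reader might infer bias, since the second booster session and the T1 measurement both fall at about 6 months. No section says that the two visits are combined.

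**Conclusion.** The mismatch holds for alpha-amylase. The protocol states a purpose for the meal and drink data, and its covariate rule and named models do not fulfil that purpose. With randomised groups the consequence is lost precision in the time x group test for this outcome, not a biased comparison, provided intake before sampling does not differ systematically by arm. The loss cannot be sized from the document. It could be nil relative to the plan (Case B), or a drop in power from 0.802 to about 0.76 to 0.69 for an assumed 10% to 30% of added variance (Case A). The point is modest, but the data are already being collected for this use, so the gain is almost free.

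The two descriptions of the saliva setting are a genuine inconsistency. It bears on this point because on-site and home collection imply different sampling conditions to record and adjust for.

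**What to change.** 1. **Statistical methods:** exempt alpha-amylase from the demographic-only covariate rule. Replace its outcome-specific repeated-measures ANOVA with a linear mixed model containing time, group and time x group, plus prespecified visit-level covariates: food or drink in the last 2 h and, if it is recorded, sampling time. These covariates should enter whatever their observed correlation with the outcome or balance between arms.
2. **Reporting:** give the same mixed model without the visit-level covariates alongside. The T1 and T2 values are measured after randomisation and could in principle be influenced by the training, so the reader should see both results. This is the small downside of adjusting.
3. **Saliva setting:** reconcile Data collection (on site, by a nurse) with Physiological measures (kept in the participant's own refrigerator or freezer), and state where samples are taken at each wave.

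The cost is a few sentences in the statistical section, one clarification of the sampling procedure and one extra line of results. No additional visits, samples or questions are needed.

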#### Employees

Regarding the assessment of employees, seven validated questionnaires and various single-item measures will be used. Employees receive an email with a link that leads to the described questionnaires. Depending on how they wish to proceed or what is most convenient for the employees, they can fill it in at home or at work.

